**Methods:**

This study is a randomized control trial, which involves a systematic review of literature of the preferred data elements regarding a DPHR, and reevaluating the results with the opinions of local endocrinologists. Inclusion criteria were as follows: type 2 diabetic patients between 20-70 of age who live in the Mashhad City and having the disease for at least one year. The sample size is 72 people that were randomly assigned to the control and intervention groups. The participants in the intervention group were allowed access to the Web-based DPHR system, while those in the control group will continue to receive the usual care for 4 months. The study primary outcome measures include self-care status of participants and planned visit adherence.

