### Trial Population and Recruitment Procedure

The inclusion criteria for participants are as follows: the patient must be a male or female with type 2 diabetes, age between 20 and 70 years, with a minimum diabetes history of one year (according to the primary diagnosis date), must live in the city of Mashhad, must be fairly computer literate, and have access to the Internet. The included participants must be able to provide informed consent.

We excluded the already included participants, if they, for any reason, decided to terminate the participation, or were unable to actively continue the required cooperation, due to sickness, pregnancy, and etc.

The trial will be conducted in Mashhad City (Iran), with participants being recruited from one endocrinology practice unit. The number of diabetic patients is estimated to be above 120,000 in Mashhad [29]. We will start the study with the acquisition of baseline information including age, education level, gender, self-care score, HbA1c, weight, employment status, length of disease, and diagnosis date along with the information required to check the inclusion eligibility. Only the qualified participants will be given the consent form.

After signing the consent form, participants will be randomized into either the intervention or the control arm. After providing confirmed consent, a package including a copy of the consent form, welcome letter, and a take-home manual, along with step-by-step directions for using the website will be rendered manually to the participants. The participants are allowed to communicate with the trial team through email or telephone, sharing their questions and concerns. For assuring the quality of trial, the trial assistant will be trained during several sessions regarding the interaction with the website, the potential questions and answers of the participants, and the intervention process.

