### Outcome Measure

The investigators will employ the Summary of Diabetes Self-care Activities Measure-revised for assessing self-care behaviors [34]. A study has reported the validity and reliability of this instrument, with an internal consistency of 0.47 and a correlation of 0.4 [34]. Also, the patient adherence to a planned visit will be measured.

In this study, researchers will examine any potential correlation, rather than cause and effect, between the app usage and the diabetes follow-up clinical indicators. Such indicators which are based on the routine follow-up procedure of diabetes clinics are: fasting blood sugar (FBS); 2-hour postprandial blood sugar; bedtime blood sugar; blood pressure; weight; height; BMI; lipid profile (total cholesterol, triglyceride, HDL, and LDL); and HbA1c.

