### Analysis Plan

All analyses will be 2-tailed and statistical significance is considered as a *P* value of ≤.05. Data will be analyzed using SPSS. χ^2^ test will be used for determining differences in subject groups based on data collected from baseline, and postintervention (significance interval of 95% will be considered). A *t* test will be used to compare the control and intervention groups, while a chi-square test will be used for continuous and categorical variables, respectively. The distribution of variables, website usage statistics, and website user satisfaction are examined using descriptive analysis.

Examination of the impact of the DPHR tool on self-care will be performed using a linear mixed model at the end of the trial period. The longitudinal nature of data collection will result in a repeat in the measure of analysis of variance using data from all trial assessment points. Missing values will be handled using multiple imputation [35]. All analyses will be done according to intention-to-treat principle.

Before inferential analysis, the homogeneity of variances of distributions in the study groups will be confirmed. The sequential logistic regression will be used for adjusting baseline characteristics and possible confounders. Dropouts from the study will be measured by no-use of the app tool for more than one month. Also, participants in the intervention group must enter blood glucose measurements at home (FBS, bedtime, 2 hours after lunch, and 2 hours after dinner) at least four times a week, otherwise, they are eliminated from the trial. The access data will be assessed using the Web server access log.

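### The only covariate adjustment named is sequential logistic regression, with no outcome stated; it does not fit the self-care score, which is analysed by a linear mixed model

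*Protocol article*

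**What the plan says.** All of the relevant analysis text is in the protocol article's Analysis Plan. On the treatment effect it says that analysis of self-care "will be performed using a linear mixed model at the end of the trial period". A further sentence adds a repeated-measures analysis that uses the measurements from every assessment, which under Study Design means baseline and post-intervention. On adjustment it says only: "The sequential logistic regression will be used for adjusting baseline characteristics and possible confounders". No dependent variable is named for the logistic model, and no other covariate adjustment is described.

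On the nature of the outcome, Outcome Measure says: "The investigators will employ the Summary of Diabetes Self-care Activities Measure-revised for assessing self-care behaviors". Trial Population and Recruitment Procedure lists the baseline items, among them "age, education level, gender, self-care score, HbA1c, weight, employment status, length of disease". No section gives a cut-point or a binary version of self-care.

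The abstract names a second outcome: "The study primary outcome measures include self-care status of participants and planned visit adherence". Randomization and Blinding states that allocation takes account of gender, employment status and age group.

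**The concern.** A binary logistic model needs a two-category outcome. Self-care is a score, and the plan itself treats it as continuous by giving it a linear model. So the one adjustment method named in the article is of the wrong type for the outcome on which the trial's hypothesis rests.

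Two things are at stake. First, the allocation factors have no stated route into the self-care analysis. When factors are balanced by design and relate to the outcome, leaving them out of the model wastes precision and tends to give standard errors that are too large. Second, an analyst who tried to follow the sentence for self-care would have to choose a threshold after the fact. The result would be an odds ratio that could not be set beside the mean difference from the mixed model.

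Sequential entry adds a smaller problem. It can produce a series of adjusted estimates, and the article does not say which of them counts.

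**Working it through.** The plan gives no figure on this point to reproduce, so the check is mainly a comparison of its statements.

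**Step 1. Match model to outcome.**

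| Outcome | Type as described | Model stated | Adjustment that could apply as written |
|---|---|---|---|
| Self-care | Score | Linear mixed model, repeated measures | None: logistic regression does not fit |
| Clinical indicators (glucose, blood pressure, lipids, HbA1c, BMI) | Continuous | Examined for correlation with app use | None: logistic regression does not fit |
| Planned visit adherence | Not stated; binary if recorded as attended or not | Not stated | Logistic regression could fit |

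The logistic sentence therefore has at most one natural home among the listed outcomes, and that is not self-care. If it is meant for visit adherence, self-care has no stated covariate adjustment. If it is meant for self-care, a cut-point is needed and is absent.

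**Step 2. Does baseline self-care already enter?** In part. If both assessments are responses in the mixed model, the baseline score is used. How it is used depends on the baseline means. With two time points and complete data, separate baseline means per arm give the difference in mean change. A common baseline mean gives, in effect, the baseline-adjusted difference. With equal variances and correlation ρ between the two scores, the variances relative to comparing 4-month scores alone are:

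- change score: 2(1 − ρ)
- baseline-adjusted: 1 − ρ²
- difference: 2(1 − ρ) − (1 − ρ²) = (1 − ρ)², which is never negative.

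The baseline-adjusted form is thus never less precise, so the text should say which is meant. The article gives no ρ, so no numerical gain is claimed.

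**Step 3. What would a cut-point cost, if one were used?** Assume a normal score and a cut c standard deviations from the centre. The efficiency relative to the linear analysis is φ(c)² / [Φ(c)(1 − Φ(c))].

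- c = 0 (median): 0.3989² / 0.25 = 2/π = 0.637, a loss of 36%
- c = 0.5: 0.581, a loss of 42%
- c = 1: 0.439, a loss of 56%

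Sample-size formulae for standardised effects from 0.3 to 1.0 give a loss of 36% to 38% at the median. The median is the most favourable of these cuts. Normality and the cut are both assumptions; neither is in the article.

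**The case against.** The strongest reply is that the article never assigns logistic regression to the self-care score. It gives self-care to a linear mixed model, and the logistic sentence may be meant for visit adherence. That is a fair reading, and it limits the point: this is a method without a stated outcome, not a plan to dichotomise. It does not remove the point, because on that reading self-care is left with no stated covariate adjustment.

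A reader might go further and infer that the trial loses about a third of its information, or that power falls from 80% to about 60%. The documents do not support this. No cut-point is planned. The power figure also needs an effect size that the Sample Size section does not give and that has to be back-solved from 30 per arm at 80% power (about 0.72 standard deviations). Even then the result depends on the test: about 59% by formula and 66% by simulation of the likelihood-ratio test. An ordinal logistic model, moreover, would avoid a two-way split.

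A reader might also infer a false-positive rate of about 13% from testing the same hypothesis in several ways. That figure rests on a median-split test and a baseline-adjusted analysis that the article does not list, and on a correlation it does not state. It is not a finding about this sentence.

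Two further replies stand in part. Omitting covariates from a randomised comparison costs precision, not validity. And a condensed article may leave covariate lists and order of entry to a fuller document. But the defect here is a named method of the wrong type for the main outcome, which a later plan following the article would carry forward.

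**Conclusion.** The point holds in a limited form. The article's only adjustment method names no outcome and does not match the continuous self-care score that the same section analyses by a linear model. As the text stands, gender, employment status and age group are used in allocation but not carried into the self-care analysis.

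The cost is some lost precision and an ambiguous adjusted result. Its size cannot be computed from the article, which gives neither the baseline-to-follow-up correlation nor the prognostic strength of the allocation factors. The 36% loss applies only if the score were split at its median, and only under normality. The matter should be corrected, but it is below must-fix, since the unadjusted randomised comparison would still be valid.

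**What to change.** Replace the logistic regression sentence with wording such as:

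> The effect on self-care is estimated from a linear model for the 4-month score, with baseline self-care score, gender, employment status and age entered together as prespecified covariates. Logistic regression is used only for binary outcomes, such as planned-visit attendance if recorded as attended or not, with the allocation factors entered together as covariates.

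If the mixed model is kept, the matching wording is: baseline and 4-month scores are both responses, the arms share a common baseline mean, and gender, employment status and age are fixed effects. The text should commit to one of the two forms, so that baseline is not both a response and a covariate.

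Drop sequential entry, so that there is one adjusted estimate per outcome. Every covariate is already collected at baseline, so the cost is analysis wording alone. The article reports recruitment as still under way, which leaves room to make the change before any outcome is analysed.

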### Study Design

A four-phase approach, including a systematic review of evidence regarding DPHR development, usability testing, iterative refinement, and intervention evaluation will be utilized. A randomized controlled trial (RCT) with a 2-arm parallel design and allocation ratio of 1:1 will be used to evaluate the impact of DPHRs on self-care. Repeated assessments will be conducted at two time points, including baseline and postintervention, over a 4-month trial period. The patients in the intervention group will be allowed access to the Web-based app, while those in the control group will be receiving usual care throughout the study period.

The DPHR interface will be designed in three types, covering our three groups of users including the participating patients, the clinic staff, and the physicians. The chief researcher will be the system administrator. Reminders via a short message service (SMS), telephone contact, and email will be used for visiting the website.

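### The plan promises intention-to-treat but eliminates low app users, and defines dropout by app non-use, in the intervention arm only; this could bias the self-care comparison towards the app

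*Protocol article*

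**What the plan says.** Three statements in the Analysis Plan section of the protocol article bear on who is analysed.

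- The principle: "All analyses will be done according to intention-to-treat principle".
- The dropout definition: "Dropouts from the study will be measured by no-use of the app tool for more than one month".
- The elimination rule: "participants in the intervention group must enter blood glucose measurements at home", and this must happen "at least four times a week, otherwise, they are eliminated from the trial".

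The same section says "Missing values will be handled using multiple imputation", without saying whether eliminated patients are among those imputed.

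The Study Design section settles who has the app: "The patients in the intervention group will be allowed access to the Web-based app, while those in the control group will be receiving usual care".

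The Trial Population and Recruitment Procedure section adds a further removal after inclusion: "We excluded the already included participants, if they, for any reason, decided to terminate the participation". It extends this to patients who can no longer cooperate, for example through illness or pregnancy. This rule covers both arms and does not depend on app use.

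**The concern.** Removing randomised patients for poor adherence is what intention-to-treat rules out. The article does not present the rule as defining a per-protocol set, and it does not say that eliminated patients are still followed up. The two statements cannot both be carried out as written.

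The rules also work on one side only. A control cannot fail a glucose-entry requirement in an app that he or she does not have, and cannot be a dropout under a definition based on using it.

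The criterion may also be related to the outcome. The study's hypothesis concerns self-care, and the Introduction lists blood glucose monitoring among the bases of diabetes self-management. Patients who enter few values may therefore be those with poorer self-care. If so, the comparison becomes one of the more diligent app users against all controls, and some of an observed difference could be selection and not an effect of the record.

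**Working it through.** **Inputs from the article.** Two-sided significance level 0.05 (Analysis Plan). Base sample size 60, dropout allowance 20%, total 72, 36 per arm (Sample Size). The stated total is reproduced by 60 × 1.20 = 72. It is used here only to fix 36 per arm; the point does not rest on it.

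**Inputs assumed.** The article gives neither the share q of the intervention arm that would be eliminated nor the correlation ρ between app use and follow-up self-care. I take q from 20% to 40% and ρ from 0.3 to 0.5, with no true effect of the app. The lower q equals the article's own dropout allowance.

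**Step 1: follow-up scores only.** If the lowest fraction q on app use is removed from one arm, the mean of those who remain shifts by

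bias = ρ × φ(z_q) / (1 − q), in SD units,

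where φ is the standard normal density and z_q its q-quantile. The factor φ(z_q)/(1 − q) is 0.350 for q = 0.2, 0.497 for q = 0.3 and 0.644 for q = 0.4. Null trials were simulated as a check (36 per arm, 40,000 runs per setting, two-sample t test):

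| Removed | ρ | Bias, formula | Bias, simulated | False-positive rate |
|---|---|---|---|---|
| 20% (7 of 36) | 0.3 | 0.105 | 0.103 | 7.1% |
| 20% (7 of 36) | 0.5 | 0.175 | 0.166 | 10.4% |
| 30% (11 of 36) | 0.3 | 0.149 | 0.147 | 8.8% |
| 30% (11 of 36) | 0.5 | 0.248 | 0.248 | 16.3% |
| 40% (14 of 36) | 0.3 | 0.193 | 0.185 | 10.4% |
| 40% (14 of 36) | 0.5 | 0.322 | 0.305 | 20.5% |

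The simulated bias is slightly lower at 20% and 40%, partly because 7/36 = 19.4% and 14/36 = 38.9%. With ρ = 0 there is no bias and the error rate stays near 5%. With all 36 + 36 patients analysed as randomised, it is 4.7–5.1% in every setting.

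**Step 2: using the baseline score.** The article plans a baseline self-care score and a linear mixed model on all assessment points, so Step 1 may not describe the main analysis. Write m = φ(z_q)/(1 − q), and assume a baseline-to-follow-up correlation of 0.5.

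- *Stable trait, baseline-adjusted.* If app use correlates ρ with both scores, both shift by ρm. The adjusted bias is ρm − 0.5 × ρm = 0.5ρm. This runs from 0.5 × 0.105 = 0.05 SD to 0.5 × 0.322 = 0.16 SD. The simulated false-positive rate is about 6–10%.
- *Stable trait, change from baseline.* The bias is ρm − ρm = 0, and the error rate is about 5%.
- *App use related to follow-up self-care but not to baseline.* The baseline mean does not shift, so nothing is subtracted. The bias is ρm again, the full size of Step 1.

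**The case against.** The strongest objection is that the follow-up-only t test is not the analysis named for the effect on self-care. The linear mixed model uses the baseline score as well, and if low app use only marks patients who already had poorer self-care, most or all of the bias goes. This stands, and the upper figures in Step 1 should not be quoted alone. It does not remove the problem. The same section also lists a t test between the groups. Moreover, patients whose self-care worsens during the trial may be the ones who stop entering values, and baseline data cannot correct for that.

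Secondly, the direction of bias is an inference. The article reports no correlation between app use and self-care. It names the self-care instrument without listing its items, and a patient may measure glucose without entering it. The Introduction makes the direction plausible, not certain.

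Thirdly, multiple imputation might help. A reader might infer that it cannot, but baseline scores and server access logs could inform an imputation for eliminated patients. This works only if those patients stay in the analysis set, which the article leaves open.

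Two further inferences go beyond the text. One is that attrition cannot be compared between arms: withdrawals and completed questionnaires can be counted in both. The other is that only retained users answer the closing opinion questionnaire: the Data Collection section refers to the participants generally.

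Finally, elimination might mean only loss of app access. The wording says the trial, so the article needs to state which is meant.

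**Conclusion.** The contradiction is certain: the intention-to-treat commitment and the elimination rule conflict, and the rule and the dropout definition can apply to the intervention arm only. The both-arm exclusions under Trial Population and Recruitment Procedure are no counterpart, because they do not turn on app use; excluding included patients for any reason adds to the conflict.

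The bias towards the app is possible and plausible, but its size is unknown. The ranges in the working rest on assumed elimination shares and correlations and on there being no true effect. Across them the bias runs from about zero (change from baseline, stable trait), through 0.05–0.16 SD (baseline-adjusted, stable trait), to 0.10–0.31 SD (follow-up only, or app use predicting follow-up self-care independently of baseline). A reader might infer that a positive result would be mostly or wholly selection. The documents do not support that; they support only that selection could not be ruled out as a contributor. That is enough to require correction before analysis.

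**What to change.** Reconcile the statements in the Analysis Plan section as follows.

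- Record app non-use and low glucose entry as measures of adherence, not as grounds for removal from follow-up or analysis. Whether such patients keep using the app is for the investigators; the point here concerns only measurement and analysis.
- Define dropout identically in both arms as a missing 4-month self-care questionnaire.
- Seek that questionnaire from all 72 randomised patients who have not withdrawn consent for data, whatever their app use. Analyse them in their randomised arm, with multiple imputation for those still missing.
- In the Trial Population and Recruitment Procedure section, separate stopping the intervention from withdrawing consent for the use of data.
- Label any analysis restricted to adherent users as supplementary and per-protocol.

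The cost is a change of wording, some extra contact with patients who stopped using the app, and possibly a smaller effect estimate. The article reports recruitment as ongoing, so this follow-up could still be arranged at that stage; outcomes not collected at 4 months cannot be recovered later. Validity still depends on obtaining outcomes from nearly everyone, or on a defensible imputation model for the rest.

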## Results

The recruitment of participants is still ongoing and preliminary results will be published in early 2016.

## Discussion

### New Insights for the App

The results from this trial will propose new insights on the app of DPHRs for patient involvement and participation with their care process. Initially in this trial, we will identify the most important data elements to consider in the design of a Web-based tool for improvement of self-care activities related to diabetes patients and then we will assess the effect of this systematically developed tool.

These trial findings will be of great help and usefulness to endocrinologists who are currently facing the challenge of timely and rapid treatment decision making in the ambulatory settings. The results are likely to be generalizable to other ambulatory endocrine/diabetes centers.

It is envisaged that results from this trial could improve diabetes patients in terms of self-care activities. In addition, our results might be used as a basis in further similar research aiming at patient empowerment using Web-based tools.

The strengths of our trial design are the evidence-based development process of the DPHR tool (based on a systematic review), the inclusion of local experts’ opinions, and the eventual refinement of the adopted design using the usability techniques. Both the value of evidence-based content development and the importance of usability testing in the app development process have been emphasized in several studies [36-38], pointing to the facts that such considerations have rarely been used across similar works [36].

